**Fig. 4 Fig4:**
[figure not shown]
Description of the model of possible mediating variables of the Vincular Project. Source: own authorship (2023). Notes: total effect of the treatment on the investigative variable (coefficient “f”); mediated direct effect of the treatment on the investigative variable (coefficient “f’”); effect of treatment on basic psychological needs (“a” coefficients); effect of the treatment on the investigative variable, including the basic psychological needs variables (coefficients “a” and “b”)

The variables used in the models will take into account the difference between post-intervention and baseline values. The effect of the intervention on depressive symptoms will be observed directly, obtaining the total direct effect of the intervention. Subsequently, all paths for potential mediating variables will be included to determine the indirect effects of treatment on depressive symptoms. Two models will be tested: the first with the observed variables, represented by the overall PHQ-9 score and the individual autonomy, competence, and relatedness scores; and the second model, considering latent variables, corresponding to each PHQ-9 question and the basic psychological needs instrument. For statistical modeling, the “backward” selection strategy will be adopted, with a critical level of *p* ≤ 0.20 for variables to remain in the model. The following adjustment indices and cutoff points will be utilized: (a) degrees of freedom (df) ≥ 1; (b) chi-square *p*-value (X2) > 0.05; (c) ratio X2 per df < 3; (d) comparative fit index (CFI) and Tucker–Lewis index (TLI) > 0.90; (e) root mean square error of approximation (RMSEA) < 0.08; (f) RMSEA *p*-value < 0.05; and (g) standardized root mean square residual (SRMR) < 0.08 [132].

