**Methods:**

This is a randomized, controlled, blinded clinical trial with adults aged 20 to 59 years, of both sexes, with depressive symptoms. The sample was intentional and non-probabilistic and participants were allocated to a control group and an intervention group. The intervention was carried out twice a week, for 16 weeks, and consisted of face-to-face and online meetings. The activities aimed to make participants more aware of their living and health conditions, exploring 24-h movement behaviors, especially physical activity, and their relationships with depressive symptoms. The contents were different in each meeting and the activities were organized into four blocks, the first being contextualization, the second with general and specific guidelines on 24-h movement behaviors, the third with opportunities to practice physical activity in different contexts and situations, and the fourth with strategies for maintaining healthy behaviors in the short and long term. Baseline (January 2023), post-intervention (May 2023), and maintenance (November 2023) evaluations included depressive symptoms as primary outcome, and 24-h movement behaviors and basic psychological needs as secondary outcomes. The variables of autonomy, competence, and relatedness were also tested as mediators related to the effectiveness of the intervention on depressive symptoms. Depressive symptoms were measured by the Patient Health Questionnaire-9 (PHQ-9), 24-h movement behaviors by self-report and accelerometry, and basic psychological needs by the translated and adapted version of the Basic Psychological Needs in Exercise Scale (BPNES). To verify the effect of the intervention, per-protocol and intention-to-treat analyses will be conducted using generalized estimating equations (GEE). Structural equation models (SEMs) will be employed in the mediation analysis.

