### Assessments

The assessment of the variables of interest was carried out at three moments: (a) baseline pre-intervention (January 2023); (b) post-intervention, immediately following the conclusion of the program (May 2023); and (c) post-intervention, 6 months after the end of the intervention (follow-up evaluation, conducted in November 2023). Questionnaires were employed to measure the variables, and participants were required to respond in the presence of a previously trained researcher. To facilitate this process, specific dates and times were scheduled based on participants’ availability. Furthermore, during these assessment periods, participants used accelerometers to objectively measure their 24-h movement behaviors. In Fig. 1, it is possible to observe a schematic diagram with the time schedule of enrolment, interventions, and assessments.

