To investigate the mediating role of basic psychological needs, structural equation modeling procedures will be adopted, using linear regression models, through the lavaan package in the RStudio software (version 2021.09.0). Diagrams will be created using the “Miro” website (https://miro.com). For the structural equation model, the “SEM” command will be utilized with the MLM estimator: maximum likelihood estimation. In this context, the mediating variable corresponds to an intervening factor essential for completing the causal relationship between an independent variable and a target behavior [129]. In intervention studies, a variable is considered a mediator when it alters the positive relationship between the treatment and the investigative variable (exemplified, in the present study, by the CG and IG and by depressive symptoms, respectively). Different analyses can be employed to identify mediating variables, based on statistical procedures that test the hypothesis that an independent variable (treatment) influences a certain outcome (investigative variable) through one or more mediators [130]. For this type of analysis to occur, a causal chain with at least three variables (independent, mediating, and dependent) is necessary, as illustrated in Fig. 3. In this model, the independent variable (treatment) is represented by “X,” while the mediating variable is “M,” and the dependent/investigative variable, “Y.” Thus, the model assumes a system with different possibilities: (a) the treatment impacting the investigative variable, referred to as the total effect (represented by coefficient “c”); (b) the treatment impacting the mediating variable (coefficient “a”); (c) the mediating variable impacting the dependent/investigative variable, with adjustment for the treatment variable (coefficient “b”); and (d) the treatment impacting the investigative variable, adjusting for the mediating variable, known as direct effect (coefficient “c”). The indirect effect of the treatment on the investigative variable through the mediating variable is calculated as the product of coefficients “a” and “b.” The total effect is calculated by summing the direct and indirect effects (c = c’ + ab) [130].

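### The mediation model relates changes in needs and in PHQ-9 over one shared interval, so a significant a×b cannot by itself show that the needs mediate the effect

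*Protocol article*

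**What the plan says.** The section on data treatment and statistical analyses, in the text after Fig. 4, fixes the form of the variables: "The variables used in the models will take into account the difference between post-intervention and baseline values". It plans two models. One uses latent variables built from the single items. The other is described as "the first with the observed variables, represented by the overall PHQ-9 score and the individual autonomy, competence, and relatedness scores".

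Earlier in the same section a mediator is defined as "an intervening factor essential for completing the causal relationship between an independent variable and a target behavior", and the text adds that "a causal chain with at least three variables (independent, mediating, and dependent) is necessary". The indirect effect of treatment is the product of paths a (treatment to needs) and b (needs to PHQ-9, adjusted for treatment).

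The statement of aims makes the mediating role of the needs a secondary objective, and the Discussion presents it as the route to understanding how change comes about.

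The abstract shows a third time point: "Baseline (January 2023), post-intervention (May 2023), and maintenance (November 2023) evaluations included depressive symptoms as primary outcome". It lists the needs among the secondary outcomes of the same evaluations. The mediation text does not use November, does not place needs change before PHQ-9 change, and does not test the reverse order. The limitations do not mention this.

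**The concern.** A causal chain from treatment to needs to depressive symptoms implies an order in time. If needs and PHQ-9 change are both taken from January to May, the data contain no such order. Randomization protects path a and the total effect. It does not protect path b, because nobody was randomized to a level of needs satisfaction.

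The reverse path is credible on the protocol's own account. The Introduction describes loss of motivation and interest as part of the illness, and PHQ-9 items cover worthlessness, anhedonia and low energy. Relief of these could itself raise felt competence or autonomy. The planned model would count that as mediation, and a secondary objective of the trial would rest on it.

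**Working it through.** **Sample sizes used below.** The protocol gives no figure for the mediation analysis, only 28 participants, doubled to 56 for dropout of up to 50%. Both reproduce. With f = 0.25, 2 groups, 3 times, and assumed correlation 0.5 and sphericity, λ = f²·N·m/(1−ρ) = 0.0625 × 28 × 3 / 0.5 = 10.5 on 2 and 52 degrees of freedom. Power is 0.812, and 28/(1 − 0.5) = 56.

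**Which interval.** The Assessments section calls both May and November post-intervention. The abstract and the planned pre/post comparison make May the natural reading. On either reading mediator and outcome share one interval.

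**What the planned model returns when there is no mediation.** Write X for arm, ΔY for PHQ-9 change and ΔM for needs change. Assume ΔY = cX + e and ΔM = γΔY + u, with c = −0.8, γ = −0.5, Var(e) = 1 and Var(u) = 0.75. These values are assumptions. The needs have no effect on depression.

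- Var(ΔM | X) = γ² + 0.75 = 0.25 + 0.75 = 1
- a = γc = (−0.5)(−0.8) = 0.40
- b = Cov(ΔM, ΔY | X) / Var(ΔM | X) = −0.5 / 1 = −0.50
- ab = 0.40 × (−0.50) = −0.20, which is 0.20/0.80 = 25% of the total effect

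Simulation agrees (N = 56: a = 0.405, b = −0.499, ab = −0.202). None of these expected values depends on N, so a larger sample only makes the false indirect effect more significant.

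**How often a and b are both significant, with no needs-to-depression effect:**

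| Assumptions (γ = −0.5, one mediator) | N = 28 | N = 56 | Very large N |
|---|---|---|---|
| Effect 0.8 SD, as above | 15% | 34% | 100% (N = 100,000) |
| Other simulations in the 0.6 to 0.8 SD range | 7 to 12% | 18 to 27% | over 99% (N = 1,000) |

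The mediated share in these other simulations was about 21 to 27%.

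**Whether fit can tell the orders apart.** With the direct path kept, f(ΔM | X)·f(ΔY | X, ΔM) and f(ΔY | X)·f(ΔM | X, ΔY) are the same joint density. In simulation the two log-likelihoods differed by less than 1e-10. The same holds for three mediators if all paths and residual covariances are free. If paths are dropped or covariances fixed, fit can differ, but the difference then tests that restriction and not the direction.

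**Two possible remedies, checked.**

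- *Baseline-adjusted values in place of change scores.* Mediator and outcome stay concurrent. False mediation at N = 56 was 22 to 25%, against 18 to 20% for change scores in the same simulations.
- *May needs to November PHQ-9, adjusted for May PHQ-9, as a condition for claiming mediation.* Assume true mediation completed by May: treatment raises needs by 0.8, needs lower May PHQ-9 with coefficient −0.5, and November carries over May at 0.6. Given May PHQ-9, the path from needs to November is then zero by construction. The planned model detects this mediation in 89% of trials at N = 56 (49% at N = 28); the conditioned lagged model does so in 5% (4%). An added direct lagged effect of −0.2 raises the 5% only to about 21 to 22%. Its low false-positive rate under reverse causation (1 to 7% at N = 56) therefore says little.

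**The case against.** The strongest reply is that this is a secondary, exploratory analysis. Parts of the article speak of potential or possible mediators, and the causal-chain sentence is a general definition. That moderates the point without removing it, since the aims and the Discussion still assign the analysis a mechanistic conclusion.

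Second, the percentages come from assumed effects, a single mediator and a joint-significance test. The plan uses three mediators together, a latent-variable model and backward selection at p ≤ 0.20. This stands: the figures show direction and rough scale, not the error rate of the planned procedure.

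Third, the aim concerns mediation of the effect achieved by May. A lagged model conditioned on May PHQ-9 answers another question, namely whether needs drive further change to November. This also stands, and such a model should not be a gate.

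A reader might infer that the use of change scores is itself the fault and that baseline covariates would cure it. They would not, because the two measurements remain concurrent. The article also lists adjustment variables, so further covariates are not ruled out.

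**Conclusion.** The concern holds in this form: as specified, a significant a×b is compatible with mediation, with reverse causation, or with both, and more participants would not resolve this. Under the assumed pure reverse causation, false mediation appears in roughly 18 to 34% of trials at N = 56 and 7 to 15% at N = 28.

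A reader might go further and infer that the needs do not mediate, or that any positive result will be spurious. The documents do not support that. The same model detects true mediation well at N = 56 under the assumptions above; what it cannot do is say which situation produced the result. The randomized comparison on PHQ-9 is not touched.

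**What to change.** In the mediation part of the section on data treatment and statistical analyses:

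1. State that mediators and outcome are January-to-May changes, and that a×b from this model will be reported as an association consistent with mediation, not proof of it.
2. Fit the reverse-order model (treatment to PHQ-9 change to needs change) and report it beside the planned one.
3. Add, as a sensitivity analysis, a lagged or cross-lagged model with May needs and November PHQ-9, adjusted for January needs and January PHQ-9. Show it with and without May PHQ-9. With it, mediation completed by May is removed. Without it, that mediation is kept, but so is the possibility that May depression drove May needs.
4. Do not make the mediation claim conditional on the version adjusted for May PHQ-9.
5. Add concurrent measurement to the limitations.

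The cost is one or two extra models on data the article says were collected, and a more cautious conclusion. November estimates may be imprecise, given anticipated dropout of up to 50%. Unmeasured confounding between needs and depressive symptoms remains under every version.

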### Sample size, randomization, and allocation concealment

The sample size was calculated using G*power 3.1.9.2 software, and was based on an ANOVA model for repeated measures with three time points and two groups. Parameters included an average effect size of 0.25, statistical power of 80%, and 5% significance level for two-tailed tests, reaching a value of 28 individuals. Anticipating a potential dropout rate of up to 50%, the number calculated was doubled, bringing the total sample size to 56 individuals. Eligible individuals were randomly assigned to either the control group (CG), instructed to maintain their usual activities, or the intervention group (IG), which actively participated in the program. To ensure numerical and participant characteristic balance between groups, randomization was stratified by sex, age, and PHQ-9 score, employing a 1:1 ratio. The randomization process was executed using the online platform randomizar.org by researchers not directly involved in the intervention. The allocation list was concealed from all study evaluators.

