Another assumption of Self-Determination Theory is that the level and quality of motivation experienced by individuals during the performance of an action are determined by the perceived value of that action in satisfying three fundamental psychological needs: autonomy, competence, and relatedness [32, 34]. Autonomy refers to actions that are self-endorsed, freely chosen by the individual, leading to a sense of ownership and personal responsibility. Competence corresponds to the perception of effectiveness in interactions with the environment, of mastering and expanding your capabilities and skills, making them challenging, until personal growth is achieved. The relatedness revolves around the desire for belonging, close emotional relationships, and the need to feel accepted and respected, fostering a sense of connection and mutual concern. It is evident that these basic psychological needs are innate and intricately linked to intrinsic motivation, self-regulation, and overall well-being. They explore the processes and conditions that facilitate healthy development and effective functioning of the individual [32]. Additionally, it is highlighted that these psychological needs are interdependent, suggesting that “the satisfaction of one need supports the satisfaction of the other two needs” [34].

Whether an individual’s basic psychological needs are satisfied or frustrated depends on the extent to which the subject’s environment and relationships support or harm these needs [34, 35]. Behaviors or messages from social agents (such as health professionals, family, friends, and colleagues), who operate within an individual’s social environment, or information obtained through various channels like magazines, newspapers, or social networks, can contribute to changes in psychological needs [36]. For example, if these behaviors, messages, or content support the satisfaction of psychological needs, individuals will presumably experience their actions as autonomously motivated, enabling the engagement and/or maintenance of health behaviors [34–36].

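### Backward deletion at p ≤ 0.20, applied as written to the three pre-stated mediators in 28 to 56 people, often removes true mediators and inflates those kept; several of the fit cut-offs are also unworkable

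*Protocol article*

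**What the plan says.** The protocol article (Study variables; Data treatment and statistical analyses) names autonomy, competence and relatedness as mediators, to be considered together. The text after Fig. 4 describes two models, both built on post-intervention minus baseline differences. The first uses the PHQ-9 total and the three need scores. The second is described as "considering latent variables, corresponding to each PHQ-9 question and the basic psychological needs instrument".

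All mediator paths are entered first. Then a backward "selection strategy will be adopted, with a critical level of *p* ≤ 0.20 for variables to remain in the model". Seven fit criteria follow, starting with "a) degrees of freedom (df) ≥ 1". They include (b) chi-square p > 0.05 and (f) RMSEA p-value < 0.05.

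The section on theory says that "these psychological needs are interdependent".

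The sample size rests on an "ANOVA model for repeated measures with three time points and two groups", with "average effect size of 0.25, statistical power of 80%, and 5% significance level for two-tailed tests", "reaching a value of 28 individuals". Then: "Anticipating a potential dropout rate of up to 50%, the number calculated was doubled, bringing the total sample size to 56 individuals". No sample size, power or error rate is given for the mediation models.

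**The concern.** The three needs are hypotheses fixed in advance, so each indirect effect should be estimated and reported whatever its p-value. A p-value filter in a small sample does two things. It drops real mediators for want of power, and it keeps the others mainly when their estimates happen to be large. The reported indirect effects would then be too big, and an interval computed as if the final model had been chosen beforehand would not reflect the selection.

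The fit criteria add to the problem. One cannot be met by the theoretically complete observed-score model. One will often be failed by a correct latent model at this sample size. Two appear to exclude each other. Mediation is a stated objective and a claimed contribution of the trial, so these rules bear on a result that will be reported.

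**Working it through.** **1. The plan's own figure.** Take the within-between interaction in a repeated-measures ANOVA with f = 0.25, m = 3 time points, N = 28, and assume ρ = 0.5 and sphericity. Then λ = f²·N·m/(1 − ρ) = 0.0625 × 28 × 3 / 0.5 = 10.5 on 2 and 52 df, and power is 0.812. Allowing for 50% dropout, 28 / 0.5 = 56. Both stated numbers reproduce. They concern the ANOVA, not the mediation models.

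**2. Backward deletion.** Inputs from the protocol: N = 28 or 56, 1:1 allocation, p ≤ 0.20 to stay. Assumed, because the protocol gives no path sizes: treatment-to-mediator path a = 0.5; mediator residual correlation 0.5; three mediators with equal true path b to the outcome, in residual-SD units. Outcome change is regressed on treatment and the three mediators, and the least significant term is removed until all have p ≤ 0.20.

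| Size of b | Kept, N = 28 | Kept ÷ true b, N = 28 | Kept, N = 56 | Kept ÷ true b, N = 56 |
|---|---|---|---|---|
| 0.2 | about 41% | 2.2 | about 52% | 1.8 |
| 0.3 | 52% | 1.73 | 72% | 1.35 |
| 0.5 | about 75% | 1.30 | about 94% | 1.06 |

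At b = 0.3, at least one of the three true mediators is lost in 95% of runs at N = 28 and 79% at N = 56. With a = 0.8 and correlation 0.3 at b = 0.3, a given mediator is lost in 41% and 23%, with ratios 1.55 and 1.22. A mediator with no effect is kept in 22–24% of runs. In the unselected model the mean b equals its true value. For b = −0.2 the true indirect effect is 0.5 × (−0.2) = −0.10; the mean when kept is −0.22 at N = 28 and −0.18 at N = 56.

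**3. Degrees of freedom, observed-score model.** Five variables (treatment, three needs, PHQ-9) give 5 × 6 / 2 = 15 moments. Parameters: 1 treatment variance + 3 a paths + 3 b paths + 1 direct path + 6 mediator residual variances and covariances + 1 outcome residual variance = 15. So df = 15 − 15 = 0. Fixing the three residual covariances to zero gives df = 3. With true residual correlation 0.3 to 0.5, that model is rejected by chi-square in 60–96% of runs at N = 28 and 86–100% at N = 56.

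**4. Latent model.** There are 9 PHQ-9 and 11 BPNES items, which with treatment make 21 variables and 21 × 22 / 2 = 231 moments. Parameters: 16 free loadings (20 items less 4 markers) + 20 item residual variances + 1 treatment variance + 3 a + 3 b + 1 direct + 6 mediator residual (co)variances + 1 outcome residual variance = 51, so df = 180. That is 28 / 51 = 0.55 to 56 / 51 = 1.10 people per parameter. Fitting the true model to simulated data (assumed loadings 0.7 or 0.85) gave chi-square p ≤ 0.05, nominally 5%, as follows:

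- N = 28: about 99–100%.
- N = 42: 79–87% under plain maximum likelihood, 91% under MLM.
- N = 56: 56–63% under plain maximum likelihood, 67–69% under MLM, the planned estimator.
- N = 300: about 11%.

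The correct model met every cut-off other than (f) in at most 0.2% of samples at N = 28 and 24–37% at N = 56.

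**5. Cut-offs (b) and (f).** The usual RMSEA p-value tests close fit, RMSEA ≤ 0.05. It is the upper tail of a noncentral chi-square with noncentrality N·df·0.05². The exact-fit p is the upper tail of the central chi-square at the same statistic. The noncentral tail is always the larger, so exact-fit p > 0.05 implies close-fit p > 0.05. Example: df = 3, N = 28, noncentrality 28 × 3 × 0.0025 = 0.21; at the boundary of (b) the close-fit p is 0.063. Over df 1, 3 and 180 and N from 28 to 56 the minimum runs from 0.058 to 0.36. No model can meet both.

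**The case against.** The strongest reply is that the deletion rule may not be aimed at the needs. The text says that all mediator paths are entered and that the needs are considered simultaneously, and Study variables lists separate adjustment variables. If only those covariates face selection, the deletion and inflation results do not apply. This is possible but less natural: no covariate is named in the description of these models, and the rule refers to variables without qualification. If it is the intent, the text should say so.

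Other parts of the reply stand:

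- The sizes depend on assumed paths. With b = 0.5 at N = 56 little is lost.
- A reader might infer that chance alone decides which need mediates. That overreaches. The simulated mediators were set equal, so which one survives is bound to be random; the rule does discriminate, keeping a null mediator in 22–24% of runs against about 75–94% for b = 0.5.
- A reader might infer that df ≥ 1 always forces a path out. It does so only in the covariate-free model with freed residual covariances. One covariate predicting only PHQ-9 change adds 6 moments and 3 parameters, giving df = 3 with every path kept. The latent model is not bound by this rule. The protocol text does not say whether the covariances are freed, and Fig. 4 is not visible here.
- A reader might infer that a correct latent model is always rejected. That is nearly so at N = 28; at N = 56 it is frequent, not certain. Nor does the protocol say what follows when a cut-off is missed.
- The protocol says multiple mediation models will be explored, which partly concedes their exploratory standing.

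**Conclusion.** The concern holds on the natural reading of the selection rule. Over b = 0.2 to 0.5, with a = 0.5 and mediator correlation 0.5, a true mediator is deleted in roughly 25–59% of trials at N = 28 and 6–48% at N = 56, and the survivors are overstated by a factor between 1.06 and 2.2. These path values are assumptions.

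The df = 0 result is a count and needs no effect-size assumption, but it is limited to the covariate-free model with correlated mediator residuals. Meeting the rule there by setting those correlations to zero sits badly with the protocol's own statement that the needs are interdependent. The latent-model failure rates assume the loadings shown and a correctly specified model. The clash between (b) and (f) is certain if (f) means the close-fit test. If it instead means a test of RMSEA ≥ 0.08, the two are compatible, but a correct latent model then passes everything in 0% of samples at N = 28 and 19–27% at N = 56.

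The reach is the secondary mediation objective. The primary GEE analysis of depressive symptoms is untouched.

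**What to change.** - Keep all three needs and the direct path in the mediation model regardless of p-value. If selection was meant for adjustment covariates, say so and limit it to them.
- Fit the observed-score model with correlated mediator residuals, and apply no fit cut-offs to it when it is saturated.
- Report every indirect effect with a bootstrap confidence interval.
- Label the item-level latent model exploratory, and report its fit indices without a pass/fail rule.
- Correct cut-off (f): state which RMSEA test is meant, and the direction that indicates acceptable fit.

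The analyses are written in the future tense and no new data are needed. The cost is revised wording, a bootstrap run, and wider intervals.

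### Mediation fit criterion (f), an RMSEA p-value below 0.05, has no stated null; under the usual close-fit test it points the wrong way and cannot be met together with criterion (b)

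*Protocol article*

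**What the plan says.** The mediation models are fitted "through the lavaan package in the RStudio software" and "with the MLM estimator: maximum likelihood estimation" (Data treatment and statistical analyses). Two models are planned, one on observed scores and one on item-level latent variables. After the description of Fig. 4, the section introduces one list of fit rules: "The following adjustment indices and cutoff points will be utilized". The items that matter here are:

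- "a) degrees of freedom (df) ≥ 1"
- "b) chi-square *p*-value (X2) > 0.05"
- "e) root mean square error of approximation (RMSEA) < 0.08"
- "f) RMSEA *p*-value < 0.05"

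The remaining items are X²/df below 3, CFI and TLI above 0.90, and SRMR below 0.08. The list is joined by a plain conjunction. It gives no order of priority, does not say what happens when a model fails one item, and does not state which hypothesis the RMSEA p-value tests.

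**The concern.** The p-value normally reported with RMSEA tests whether RMSEA is at most 0.05. A small value is evidence against close fit, so a good-fit rule asks for a large one. Items (b) to (e) and (g) all reward good fit; (f) alone rewards misfit.

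Items (b) and (f) are also two p-values computed from one statistic, and they are asked to fall on opposite sides of 0.05. Mediation by autonomy, competence and relatedness is a stated secondary objective, and this list is the article's only rule for judging whether a mediation model fits. If two of its items exclude each other, the judgement of fit rests on a choice that the plan does not make.

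**Working it through.** **Inputs.** The cutoffs (a), (b), (c), (e) and (f) come from the list. N = 56 (planned total) and N = 28 (before the allowance for dropout) come from Sample size, randomization, and allocation concealment. The list contains no calculated figure to reproduce. N enters only through the noncentrality below, and the conclusion does not depend on its value.

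The article gives no degrees of freedom, so these are assumptions:

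- *Observed-score model.* Treatment, three needs scores and the PHQ-9 score give 5 × 6 / 2 = 15 moments. With uncorrelated mediator residuals there are 3 + 3 + 1 paths, 4 residual variances and 1 treatment variance, which is 12 parameters, so df = 3.
- *Item-level model.* Nine PHQ-9 items, eleven BPNES items and treatment give 21 × 22 / 2 = 231 moments. Four factors need 16 free loadings, 20 item residuals, 4 factor residuals, 7 paths and 1 treatment variance, which is 48 parameters, so df = 183. Letting the three mediator residuals correlate gives df = 180.

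**Formulas.**

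- Chi-square p-value: p_chi = P(χ²(df) > X²).
- Close-fit p-value: p_close = P(χ²(df, λ) > X²), with λ = N × df × 0.05².
- RMSEA = √[(X² − df) / (N × df)], so (e) means X² < df + N × df × 0.08².

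**General result.** A noncentral chi-square is stochastically larger than a central one with the same df, so p_close ≥ p_chi for every X², df and N. If (b) holds, then p_close ≥ p_chi > 0.05 and (f) fails. A numerical search restricted to values meeting (b), with N from 20 to 5000 and df from 1 to 200, found 0 of 129,600 points with p_close below 0.05.

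**Thresholds.**

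| N | df | (b) needs X² below | (f) needs X² above | (e) needs X² below | p_close when p_chi = 0.05 |
|---|---|---|---|---|---|
| 56 | 1 | 3.84 | 4.37 | 1.36 | 0.066 |
| 56 | 3 | 7.81 | 8.87 | 4.08 | 0.076 |
| 56 | 183 | 215.6 | 245.4 | 248.6 | 0.363 |
| 28 | 1 | 3.84 | 4.11 | 1.18 | 0.058 |
| 28 | 3 | 7.81 | 8.35 | 3.54 | 0.063 |
| 28 | 183 | 215.6 | 230.6 | 215.8 | 0.166 |

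At N = 56 and df = 3, the value at which (f) starts to hold has p_chi = 0.031 and RMSEA = √[(8.87 − 3) / (56 × 3)] = √(5.87 / 168) = 0.187, so (e) fails too. At df = 1 it also breaks (c), since 4.37 / 1 exceeds 3.

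At N = 56 and df = 180, (b) needs X² < 212.3 and (f) needs X² > 241.7 (p_chi = 0.0015). There RMSEA = √[(241.7 − 180) / (56 × 180)] = 0.078, so (e) and (f) can just coexist while (b) and (f) still cannot. Items (e) and (f) become compatible only from df = 157 at N = 56 and from df = 539 at N = 28.

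A model that fits perfectly (X² near 0) has p_close near 1 and fails (f).

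**The case against.** **The null is not named.** A test of not-close fit (null: RMSEA at least 0.08) exists and uses the same 0.08 as (e). For that test, p < 0.05 is the right direction and can coexist with (b). At N = 56 a correctly specified model would then meet (f) with probability about 0.06 at df = 1, 0.08 at df = 3 and 0.91 at df = 183. At N = 28 the figures are 0.05, 0.06 and 0.46. This stands as a reason to make the finding conditional and to ask for the null. It does not remove the finding: nothing in the article points to that test, close fit is the usual meaning, and for the observed-score model the alternative would turn away nearly every correct model.

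**The list may be meant as an overall judgement.** A reader might infer that every mediation model must be rejected. The article says the cutoffs will be used; it does not say that failing one rejects a model. That stronger statement holds only if all seven are required.

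**Poor models are not thereby let in.** A reader might also infer that badly fitting models would be retained. That does not follow, because any model that meets (f) in its close-fit sense fails (b), and at small df it fails (e) as well.

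**It may be a simple slip of sign.** That is plausible, but no other part of the article corrects it.

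**Conclusion.** Criterion (f) is wrong as written under the usual close-fit reading: the inequality is reversed, and (b) and (f) exclude each other at every N and df. If all cutoffs must be met, no mediation model can satisfy the list. Otherwise (f) counts good fit against a model, and the analyst must choose which criterion to disregard.

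This rests on two assumptions: that the RMSEA p-value is the close-fit test, and that both p-values come from the same statistic. With MLM, the second means the same scaled chi-square; the plan describes no mixing of scaled and unscaled versions. The df values only illustrate the size of the gap.

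A clash between (e) and (f) should not be claimed in general. It holds at small df, and not at df near 180 with N = 56.

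The consequence is limited. The primary PHQ-9 comparison uses GEE and is untouched. Within the mediation analysis, the fit indices screen the model; they do not estimate or test the indirect effect. This is a correction that should be made, not one on which the trial's main conclusion depends.

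**What to change.** Name the null hypothesis of the RMSEA p-value. If close fit is meant, change (f) to a close-fit RMSEA p-value above 0.05. Every model that meets (b) then also meets (f), as the last column of the table shows, so the two no longer conflict. Because (f) is then implied by (b), it can equally be deleted and RMSEA reported with its 90% confidence interval.

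The cost is one reversed sign and a short phrase, with no effect on data or sample size. Data collection is finished, but the article still describes the analyses in the future tense, so the correction can be recorded before the mediation results are reported.
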